## Abstract

**Background:**

Mental disorders are the most common reason for sick leave in Sweden. Knowledge about effective methods to help these individuals to return to work (RTW)/entry into work or studies is limited. Rehabilitation coordinators (RC’s) have been introduced within healthcare with the purpose to promote cooperation, streamline the sick leave and rehabilitation process, and facilitate RTW for sick-listed patients. The function of RC’s has shown positive results by reducing sick leave within primary healthcare. However, the function has not been evaluated in terms of specialist psychiatry. This paper describes the design of a study to evaluate effects of a RC intervention on sick leave and RTW/entry in work or studies in patients with moderate to severe affective and/or moderate to severe anxiety disorders within specialist psychiatric care.

**Methods:**

A randomised controlled trial (RCT) comparing an intervention group receiving support from a RC with a control group receiving treatment as usual (TAU). The target group is patients on sick leave, treated for affective and/or anxiety disorder, aged 25–64, with or without employment.

**Discussion:**

This study gives the possibility to evaluate a RC intervention for individuals with mental disorders. If the study has promising vocational outcomes, it may be of importance for the participants in many ways, e.g. increase participation in society, provide economic benefits and improve health and wellbeing. This would be valuable for the individual as well as for the society.

**Trial registration:**

The study is registered at the Clinicaltrials.gov Register Platform (ID NCT03729050) in 2 November 2018.

## Background

Mental disorders are a major challenge in Europe, with depression and anxiety being the most common [1]. In Sweden, mental disorders are also the most common reason for sick leave [2]. Sick leave may be necessary for healing and recovery and prove to be necessary due to the tasks required for the specific work. However, longer periods of sick leave by itself can have negative impact, including impaired health [3, 4] and reduce the possibility for return to work (RTW) [5]. Individuals with mental disorders are in general more likely to be unemployed [6]; moreover, among young individuals diagnosed with depression- or anxiety disorder (bipolar disorders not included), 20% were still outside of the labour market 10 years later [7]. Similar to long-term sick leave, unemployment at young age has also been associated with negative effects on health and well-being [8, 9]. This negative impact on health may further complicate the possibility of entering the labour market, which in a long-term perspective may lead to marginalisation and exclusion from the labour market and society for these individuals. Nonetheless, knowledge about what actions are effective in supporting individuals with mental disorders to RTW/entry work or studies is limited [10].

Longer durations of sick leave (≥60 days) increase the need for vocational rehabilitation [11], which is rehabilitation interventions aimed at facilitating RTW [12]. Hence, individuals suffering from injury or illness have the possibility to receive rehabilitation and support to get prerequisites to regain work ability [13]. Several actors can be involved in the vocational rehabilitation e.g. the Swedish Social Insurance Agency (SSIA), healthcare, employers, Swedish Public Employment Service (SPES) and the municipality [14], each having their own responsibilities [14]. Work ability can be judged differently among the actors involved in the vocational rehabilitation, which can lead to contradictions between them [15] and thus constitute an obstacle in the rehabilitation process. To reach positive RTW outcomes, it is assumed that cooperation between these actors and the individual takes place [16]. Lack of cooperation between these actors can instead complicate the individual’s ability to RTW [17]. Factors that influence the individual’s opportunity to RTW successfully include participation from the employer and support from the workplace [10]. Moreover, contact between the healthcare and the employer as well as involvement of a person who coordinates the vocational rehabilitation are important [18].

A previous meta-analysis demonstrates a clear but moderate effect on the RTW for employees who were on sick leave and who had access to a person who coordinated their vocational rehabilitation process [19]. Nonetheless, another review could not show that RTW coordination was more effective than usual practice with respect to RTW [20]. However, the RTW coordination can be carried out differently with regard to content, length and design.

In Sweden, a new function for coordination called Rehabilitation coordinator (RC) has been introduced within healthcare [21]. The purpose with RC, in addition to provide support to patients in their rehabilitation process [22], is to promote cooperation, streamline the sick leave and rehabilitation process, and facilitate RTW for sick-listed patients [21]. The RC’s performance has been developed over the last years, and the function is now available in primary care and to a certain extent within specialist healthcare [23]. One prioritised group for the RC is patients with mental disorders, i.e. F diagnoses, according to the International Classification of Disease (ICD) system [24].

The practice of RC’s has been developed and evaluated with positive outcomes [21, 25, 26] in the Swedish primary care. Nonetheless, to our knowledge, the effect of RC’s has not been investigated regarding reduced sick leave or RTW/entry in work or studies in patients with mental disorder within specialist psychiatric care.

This study protocol presents the design of a study aiming to evaluate a RC intervention for patients with mental disorder within the specialist psychiatry care. The objective of the study is to evaluate effects of a RC intervention on sick leave and RTW/entry in work or studies in patients with medium to severe affective and/or medium to severe anxiety disorders receiving treatment within specialist psychiatric care. The hypothesis is that the participants who receive the intervention will show a decrease in sick leave (extension and length) and to a higher degree have RTW/entry work or studies at 12-month follow-up, compared with participants receiving treatment as usual (TAU).

## Methods

### Study design and setting

The study is designed to be a randomised controlled trial (RCT) with an intervention group receiving support from a RC compared with a control group receiving TAU. The study will be conducted in specialist psychiatric care in a middle region of Sweden, between October 2018 and October 2021. The healthcare unit includes psychologists, physicians, nurses and social workers.

### Power calculation

The estimation of sample size was based on an outcome measure with two possible outcomes: proportion of patients who RTW/entry work or studies (positive outcome) and proportion of patients that has not RTW/entry work or studies (negative/unchanged outcome). The statistical programme Stata 15.0 has been used to estimate the study’s strength (statistical power). The power estimation was based on a two-sided 5% significance level. In order to detect a difference at 15% between the groups in the main outcome with around 80% power, at least 121 individuals in the intervention and the control group are needed, respectively.

### Participants and recruitments

The inclusion criteria are patients on sick leave, having moderate to severe affective and/or anxiety disorder (see Table 1 for ICD-codes), receiving treatment within a specialist psychiatric unit, aged 25–64 years, with or without employment. The exclusion criteria are multiple somatic illnesses, at high suicidal risk, fulltime sickness compensation (i.e. compensation for those between ages 30 and 64 who probably never will be able to work full time due to illness, injury or disability) [27], taking part in an ongoing vocational rehabilitation and being a patient outside of the county.

**Table 1 Tab1:** Diagnostic codes in accordance to the International Classification of Disease 10-SE

Disorder	ICD code
Bipolar disorder	F31.0-F31.9
Depression	F32.1-F32.3, F33.0-F33.4, F33.9
Post-traumatic stress disorder (PTSD)	F43.1
Generalized anxiety disorder	F41.1
Neuropsychiatric disorder	F84.0, F84.1, F84.4, F84.5, F90.0

The healthcare professionals within the healthcare unit can identify prospective participants for the study. Prospective participants can also be identified by the RC through a patient register called “Rehabstöd”, which is an IT-application showing all sick listed patients in the care unit. After consulting a doctor, potential participants, fulfilling the inclusion criteria and not the exclusion criteria, will be sent an invitation letter with information about the study. After 2 weeks, a research assistant will call the potential participant and provide verbal information about the study and invite him/her to participate. If the patient is interested in participating, a consent and baseline questionnaire will be mailed to the potential participant. Those willing to participate in the study must give their written consent and answer the baseline questionnaire. Thereafter, participants will be randomised to either the intervention or control group (see Fig. 1, Flow chart for recruitment process and datacollection). Randomisation will be achieved by using a computer generated list of random numbers and will not be stratified.

**Fig. 1 Fig1:**
[figure not shown]
Flow chart for recruitment process and data collection

### Intervention

#### Description of education and training of the RC

The RC undergoes an online course for rehabilitation coordination according to the Swedish Association of Local Authorities and Regions (SALAR). Except for an introduction about the overview of the mission and goal of the RC’s function, the course includes the following areas: *support to the patient*, *internal coordination and collaboration*, *external collaboration* and *patient cases.* Further, an online course in Insurance Medicine is obtained by the SALAR. The Insurance medicine team in the region will provide continuous competence development and process support. The RC will be given the opportunity to participate in a network together with the primary care RC’s and national network meetings for RC’s working in psychiatric care. Since RC is a new function in the specialist psychiatric care, which differs from primary care, the needs and assignments must be adapted thereto. Regular follow-up meetings will therefore take place with the process leader in the Insurance medical team to follow how the work model performs and whether something needs to be adjusted and/or clarified in the assignment.

#### Rehabilitation coordinator intervention

The RC meets the patients at the unit and assesses rehabilitation needs that are relevant for the ability to RTW/entry into work or studies, by interviewing the patient. By mapping the patient’s rehabilitation needs, a plan for the rehabilitation can be established, focusing on RTW/entry in work or studies. The RC constitutes a contact person for the participant, provides individualised support, and can initiate and coordinate contacts within- (healthcare professionals) and outside of healthcare (e.g. the SSIA, the SPES, the municipality, and the potential employer) needed for the RTW process. The RC intervention is estimated to last for approximately 1 year for patients randomised to the intervention group.

#### Strategies to improve adherence to intervention and procedures for monitoring adherence

RC’s adherence to the working method can be studied through documentation in the patient’s medical record, where the given efforts provided must be documented. The RC’s will work in accordance with the mission for RC’s described in the *Method book for coordination of sick leave and rehabilitation for healthcare* [28]. The method is organised in different levels; however, in this study, the RC will not include all these levels in the intervention. The RC’s access to the method book and contact with the process leader should be sufficient to comply with the working method.

### Control group

The control group receives TAU i.e. standard treatment at the healthcare unit and can include psychological therapy either individually or in groups, medical treatment, and psychosocial efforts. The psychosocial efforts can include support to ensure the patient’s financial security and efforts to support RTW/entry in work or studies. For description of the content in the RC intervention respectively control group, see Table 2).

**Table 2 Tab2:** Description of content in the RC intervention respectively control group

RC intervention^a^	Control group
The RC - assesses the participant’s need for rehabilitation, - develops a plan for RTW/entry into work or studies together with the patient, - constitutes contact person for the participant, - provides individualised support - initiates and coordinates contacts within and outside of healthcare.	TAU can include; - psychological therapy either individually or in groups, - medical treatment - psychosocial efforts (e.g. support to ensure the patient’s financial security and efforts to support RTW/entry in work or studies)

^a^Includes TAU

### Data collection

Data will be collected from registers, medical records and questionnaires. Registry data will be collected from the SSIA’s Micro Data for the Analysis of Social Insurance Agency register (MiDAS) and the Longitudinal Integration Database for Health Insurance and Labour Market Studies (LISA) administrated by Statistics Sweden (SCB) and Easit (system for ordering information on healthcare consumption). Data regarding diagnosis (at baseline) and information about efforts/contributions and efforts by the healthcare and the RC (intervention group) will be collected through medical records, for both the intervention- and control group. Questionnaire data will be collected at baseline, 6 and 12 months. See Fig. 1 for information about the recruitment process and data collection.

### Outcome measures

The primary outcomes of the study is to evaluate effects of the RC intervention. We will analyse the difference between the intervention group and the controls in proportion of patients 1) on full- or part-time sick leave (extension) and time on sick leave (length) and 2) who RTW/entry into work or studies at 12 months.

Secondary outcomes are to perform analysis concerning workability, health outcomes and care consumption between the intervention group and the control group.

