#### Registered sick leave and RTW/entry in work or studies

Primary outcomes will be measured with registry data from MiDAS and SCB. MiDAS includes information about sick leave, extension and length, and previous sick leave periods. Full- or part-time is measured as sick leave on 25/50/75% or full-time (100%) and length. LISA includes information about income (salary, remuneration via the SPES or the municipality, reimbursement/grant for studies, remuneration via the SSIA). RTW/entry into work or studies is defined as any kind of activities such as: job training, traineeships or part or full-time employment with wages or benefits, or part or full-time studies. The analyses will be performed between- and within groups 12 months after inclusion, with the possibility of a follow-up at 24 months.

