### Data management and analysis

All participants will receive a code and data will be depersonalized. The linking code will be kept separate from the research data. All data will be storage in an electronic security-classified storage area. Measures to prevent loss of data will be taken through the use of automatic back-up routines implemented in the storage system. Access to data will be restricted to the research personnel working directly with data entry or analyses.

Intention-to-treat analyses will be performed, and if relevant, per-protocol analyses will be conducted. The main statistical analyses will be done with regression analyses, where the effect of the intervention will be measured against the respective main outcome. Differences in proportions between the intervention and control group regarding full- or part-time sick leave and RTW/entry into work or studies will be analysed with descriptive statistics and logistic regression analyses. Linear regressions will be used to analyse differences in length of time for sick leave between the groups. The regression analyses will be adjusted for potential confounders, and missing data will be handled with multiple imputations if needed. Data will be analysed using Statistical Package for the Social Sciences, SPSS, version (IBM, Corporation, Armonk, New York, USA). A significance level of *p* < 0.05 will be considered statistically significant.

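### Three unranked primary outcomes are each tested at 5% in a trial sized on one, with no rule for success, so either the 5% error rate or the 80% power is lost

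*Protocol article*

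**What the plan says.** Four sections of the protocol article bear on this.

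- **Power calculation.** "The estimation of sample size was based on an outcome measure with two possible outcomes", namely having or not having returned to work or entered work or studies. The section treats this as the one main outcome. "The power estimation was based on a two-sided 5% significance level", and 121 per group is given for a 15-point difference with about 80% power.
- **Outcome measures.** The heading statement is plural: "The primary outcomes of the study is to evaluate effects of the RC intervention". The comparisons that follow are the proportions of patients "on full- or part-time sick leave (extension) and time on sick leave (length) and 2) who RTW/entry into work or studies at 12 months". That makes three comparisons under two numbers, with no order of importance.
- **Data management and analysis.** Each main outcome gets its own regression: logistic for full- or part-time sick leave, linear for length, logistic for RTW. The only criterion is "A significance level of *p* < 0.05 will be considered statistically significant".
- **Background (hypothesis).** Intervention participants "will show a decrease in sick leave (extension and length) and to a higher degree have RTW/entry work or studies at 12-month follow-up". The outcomes are joined by a conjunction, but this is not turned into a decision rule.

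In addition, the section on registered sick leave and RTW says: "The analyses will be performed between- and within groups 12 months after inclusion".

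**The concern.** The sample-size section describes a trial with one deciding outcome. The outcome and analysis sections describe a trial with three. The reader cannot tell whether one positive test, a particular positive test, or all three would support the claim that the rehabilitation coordinator works.

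The choice matters because the two stated operating characteristics, 5% error and about 80% power, both belong to a single RTW test. With three unranked tests, the first fails if any win is enough and the second fails if every win is needed. A mixed result, such as RTW positive and sick leave not, would leave the trial without a predefined answer.

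**Working it through.** **Inputs.** From the protocol: three primary comparisons (Outcome measures), p < 0.05 for each (Data management and analysis), and two-sided 5%, a 15-point difference, about 80% power and 121 per group (Power calculation). Not given, so assumed: the RTW rate in controls, the correlation between the three test statistics, and the power for the two sick-leave outcomes.

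**1. The plan's own figure.** With pooled variance and no continuity correction,

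n per group = [1.960 √(2 p̄(1−p̄)) + 0.842 √(p₁(1−p₁) + p₂(1−p₂))]² / (p₂−p₁)².

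With assumed rates of 15% and 30%, p̄ = 0.225 and n = (1.1575 + 0.4889)² / 0.0225 = 120.5, so 121. Power at 121 is 80.2%. The mirror pair, 70% and 85%, gives the same result. The stated size therefore reproduces as a single RTW test at 5%, with no allowance for other primary tests. Other base rates would give 76 to 174 per group.

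**2. If any one win counts.** For independent tests the family-wise error is 1 − 0.95³ = 14.3%, and the upper bound under any dependence is 3 × 5% = 15%. For three test statistics with a common correlation:

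| Correlation | P(at least one p < 0.05) with no effect |
|---|---|
| 0 | 14.3% |
| 0.3 | 13.6% |
| 0.5 | 12.5% |
| 0.7 | 10.9% |
| 0.8 | 9.8% |
| 0.9 | 8.4% |
| 0.95 | 7.4% |

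Counting only false positives in favour of the intervention, the figure is about 4% (correlation 0.9) to 7% (independent), against 2.5% for one test. If extent and length were treated as one test, two independent tests would give 1 − 0.95² = 9.75%.

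**3. If all three must succeed.** Error is not inflated. Joint power, however, cannot exceed the power of the weakest test, so it is at most the RTW power and generally lower. Assuming 80% power for each test (the protocol gives none for sick leave), joint power is 0.8³ = 51% if independent, 61% at correlation 0.5 and 69% at 0.8.

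**4. What the repairs cost in sample size.** With 15% versus 30%:

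- RTW as sole primary, or first in a fixed sequence: alpha stays 0.05, and 121 per group keeps 80.2% power.
- Bonferroni over three tests, alpha 0.05/3 = 0.0167: RTW needs 161 per group, or has 65.8% power at 121.

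**The case against.** The strongest reply is that inflation is conditional. No section says that any single win makes the trial positive, and the only stated hypothesis joins the outcomes. A reader might infer that the false positive rate is simply well above 5%, or is 14%. The document does not support that as an unconditional statement. It holds only under the any-win reading, and 14.3% also needs independence, which is unlikely for three linked outcomes measured at the same follow-up. This part of the objection stands, and the figures above are conditional for that reason.

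A second reply is that the singular main outcome in the Power calculation already shows that RTW leads, and that multiplicity rules usually sit in an analysis plan. The hint is real, but the outcome and analysis sections do not carry it through. The article is not merely silent. It fixes three primary outcomes, separate tests and one unadjusted threshold beside a sample size for one of them. An analysis plan could repair this only by adding a ranking or success rule that the article lacks.

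Two further inferences should be resisted:

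- **Within-group analyses.** A reader might infer that these are significance tests bound to come out positive, because everyone enters on sick leave. The text names no within-group test, and all regressions described compare the groups. The within-group results may be purely descriptive.
- **Contradictory outcomes in one patient.** A reader might infer that someone half at work and half on sick leave necessarily fails one primary outcome and passes another. That follows only if extent means any versus no sick leave. The article also records extent in steps of 25%, and a fall from 100% to 50% would be an improvement on that scale.

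Finally, the choice of hierarchy is partly judgement. Sick leave is listed first in the hypothesis and numbered first among the outcomes. Declared co-primaries or a Holm or Bonferroni procedure would also remove the ambiguity.

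**Conclusion.** The concern holds in a conditional form. The article gives two incompatible accounts of what is primary and no rule for success, and under neither natural rule do 5% error and about 80% power both hold.

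- **Any win suffices:** family-wise error of about 8% to 14%, for correlations from 0.9 down to 0. The correlation is not given, and positive correlation is likely, so the independent-tests value is the top of the range and not the best guess.
- **All must win:** error is controlled, but joint power falls below the stated figure. The range of 51% to 69% rests on assuming 80% power for each test and correlations of 0 to 0.8. That joint power cannot exceed the RTW power needs no assumption.

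The sample size itself is not in dispute here: 121 reproduces for one RTW test at assumed rates of 15% and 30%. Because the ambiguity concerns the trial's main conclusion, it should be settled before any outcome data are seen.

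**What to change.** Reconcile the hypothesis, Power calculation, Outcome measures and Data management and analysis sections:

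1. Name the between-group difference in RTW or entry into work or studies at 12 months as the single primary outcome, since the sample size was built on it.
2. Make sick-leave extent and sick-leave length key secondary outcomes. Test them after RTW in a fixed order stated in advance, each at two-sided 5%, stopping at the first non-significant result.
3. State that the within-group analyses are descriptive and do not support the conclusion on effectiveness.

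The change is to wording only: 121 per group and its stated power are kept. The cost is that an effect on sick leave can be claimed as confirmed only if RTW is positive, which is a real loss if the sponsor regards sick leave as equally important. In that case the alternative is to declare the co-primary rule openly and accept its price: for Bonferroni, 161 per group or 65.8% power for RTW at 121 (at 15% versus 30%).
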